##### EEG Data

EEGLab^1^ will be used for EEG data pre-processing and analysis. Independent Component Analysis (ICA) will be used for artifact rejection and IAF. IAF will be determined in the first 5 min of a 10-min run in phase in which participant will not receive any stimulation, with alternating cycles between eyes open and eyes closed. Fast Fourier Transformation (FFT) will be applied to posterior α. Power estimates will be obtained by squaring filtered EEG signals and then band power values will be averaged for both the pre-stimulus reference period and the task intervals. We will then segment the trials in blocks of 5-s, and average the brain activity for those blocks. In order to prevent the mismatch between α-tACS and measured α, α peak will be measured always during the first 5-min of the session (without training) and in the 5-min immediately after stimulation has ended (see Figure 3). Source information toolbox^2^ will be used for the coherence and connectivity analysis between the eight electrodes (FP1, FP2, C3, C4, T3, T4, O1, and O2) without pre-specifying specific Region of Interest (ROI) comparisons.

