## Abstract

Several cognitive training programs, alone or in combination with non-invasive brain stimulation have been tested in order to ameliorate age-related cognitive impairments, such as the ones found in Mild Cognitive Impairment (MCI). However, the effects of Cognitive Training (CT)—combined or not—with several forms of non-invasive brain stimulation have been modest at most. We aim to assess if Speed of Processing (SoP) training combined with alpha transcranial alternating current stimulation (α-tACS) is able to increase speed of processing as assessed by the Useful Field of View (UFOV), when comparing to SoP training or active α-tACS alone. Moreover, we want to assess if those changes in speed of processing transfer to other cognitive domains, such as memory, language and executive functioning by using the NIH EXAMINER. We also want to test the mechanisms underlying these interventions, namely brain connectivity and coherence as assessed by electroencephalography (EEG). To that purpose, our proposal is to enroll 327 elders diagnosed with MCI in a double-blinded, parallel randomized clinical trial assessing the effects of combining SoP with alpha endogenous tACS (either active or sham) in people with MCI. Participants will perform an intervention that will last for 15 sessions. For the first 3 weeks, participants will receive nine sessions of the intervention, and then will receive two sessions per week (i.e., booster) for the following 3 weeks. They will then be assessed at 1, 3, and 6 months after the intervention has ended. This will allow us to detect the immediate, and long-term effects of the interventions, as well as to probe the mechanisms underlying its effects.

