We have previously shown that we were able to modulate cognition using transcranial direct current stimulation (tDCS), namely on executive functioning (Leite et al., 2011, 2013), working memory (Carvalho et al., 2015a), empathy (Rêgo et al., 2015), approach/avoidance motivation underlying craving (Carvalho et al., 2018), attention and pain (Silva et al., 2017; Santos et al., 2018). Furthermore, by understanding the underlying mechanisms of the intervention in the brain, it is possible to develop neural based interventions, whose ultimate aim is to optimize the target engagement (Carvalho et al., 2015b).

One possible way of doing so, is to combine SoP training with another technique— transcranial alternating current stimulation (tACS) —which has been shown to entrain brain activity (Antal and Herrmann, 2016). Entrainment refers to the frequency dependent response of brain waves in order to match the frequency of the stimulus that are being applied to the brain (Huang and Charyton, 2008). Alpha entrainment may be of particular interest for SoP. For instance, a study has already showed that speed of processing is associated with changes in this specific band (Hilla et al., 2020). By combining the two interventions, it will be hypothetically possible to optimize brain communication between distal regions, and thus, increase cognitive performance. According to the Communication through Coherence hypothesis (CTC), effective connectivity requires rhythmic synchronization between pre and post synaptic neurons and their coherence. Thus, in the absence of coherence, inputs arrive at random phases of the excitability cycle, which result in lower connectivity (and efficiency; Fries, 2015). Therefore, coherence between pre and postsynaptic neurons is required for efficient communication. In the case of absence of coherence (as in the case of a “disconnected brain due to ageing), performance is impaired.

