### Outcomes

Main outcome will be the Useful Field of View (UFOV) test for speed of processing and attention (Ball et al., 1988). The UFOV is a test that was designed to evaluate daily life difficulties experienced by the elderly, such tasks that require divided visual attention and have to be undertaken rapidly (speed of processing). The four-subtest stimulus will be used for the computerized version, namely identification alone; divided attention; selective attention; selective attention in conjunction with same/different discriminations will be used (Edwards et al., 2006). UFOV is expected to be completed in 10 min and participants are asked to touch the screen as soon as they identify a target (i.e., a car silhouette inside a box), with the target exposure ranging from 16.67 to 500 ms. In order to probe divided attention, a peripheral target is added to the central target. For the selective attention, distractors are added; while for the more demanding version, there are two central targets, and participant are asked to make a judgment if they are similar or not.

The NIH EXAMINER battery will be used for assessing transfer effects of the intervention to untrained domains. The NIH EXAMINER comprises cognitive control, verbal fluency, and working memory assessments (Possin et al., 2013). Namely, NIH EXAMINER is a computerized version of several tasks targeting working memory, inhibition, set shifting, fluency, insight, planning, social cognition, and behavior, which allows for the calculation of a composite score (Kramer et al., 2014). As the time to complete several tasks is performance dependent, we expect participants to complete the NIH EXAMINER between 30 and 60 min.

Resting state EEG will be used as a surrogate outcome, and will be performed before and immediately after the intervention in order to assess power spectral density changes, cross frequency couplings and coherence among electrodes. Participants will also perform a short auditory oddball task (Fz, Cz, Pz, and Oz) because the P3 wave is a good marker of brain’s speed of processing. Analysis will be considered exploratory if the dropout rate reaches 20%.

At week 3 and 6 outcomes will be collected the following business day, due to particular characteristics of the sample.

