#### EEG Data

EEG data will be acquired using a 8-channel Loop-IT (Neurocare, Ilmenau, Germany) following the 10/20 system, in a continuous mode at a digitization rate of 500 Hz, with a bandpass filter of 0.01–100 Hz. The EOG will be recorded from two additional bipolar channels. Electrode impedances will be kept below 5 kΩ. We will be especially interested in changes in α- power, P300 from the oddball task, Event Related Desynchronization (ERD; for alpha attenuation) and Phase amplitude coupling (PAC; mainly α−γ).

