This proposal has some ethical concerns that need to be addressed according to national and international regulations. The participation of subjects will always be informed, consented and voluntary. If participants are vulnerable individuals or groups then research activities will only be performed if all potential risks are minimized, and the outcome of research is valuable enough that can have an impact in their quality of life, mental health or well-being. The current proposal involves the use of physical techniques, which are not invasive and do not represent more than minimal risk.

Therefore, the current proposal aims at combining speed of processing training (SoP) with endogenous alpha tACS, by developing an EEG-tACS closed loop solution. Additionally, we plan to use executive measures to assess if speed of processing training transfers to other higher order cognitive domains. Furthermore, we want to explore how changes in cognition are related to changes in the brain, as assessed by the EEG, namely connectivity across proximal and distal regions, and coupling with other frequencies of interest, such as the alpha-gamma amplitude coupling. In sum, the results of this project will further provide important insights into the mechanisms underlying EEG-tACS closed-loop coupled with cognitive training to enhance Speed of Processing in people with MCI. This proposal will allow us to test a new intervention, at the same time that we explore the mechanism by which the intervention works, and to probe for potential biomarkers that may be useful to guide future interventions.

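### Coherence between scalp electrodes is the only connectivity measure named, with no stated control for shared pickup or alpha power, so a rise would be ambiguous as evidence of better communication

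*Protocol article*

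**What the plan says.** The Abstract makes brain connectivity and coherence, measured by EEG, the mechanistic aim. Under Outcomes, resting EEG is to assess "power spectral density changes, cross frequency couplings and coherence among electrodes". In Statistical Analysis, EEG Data, a toolbox "will be used for the coherence and connectivity analysis between the eight electrodes", which are then listed, "without pre-specifying specific Region of Interest (ROI) comparisons". The same section gives ICA two uses, artifact rejection and finding the individual alpha frequency. In Assessments, EEG Data, the montage is fixed ("EEG data will be acquired using a 8-channel Loop-IT") and alpha power is an outcome in its own right: "We will be especially interested in changes in α- power".

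The planned interpretation goes further than the scalp. The Introduction holds that "effective connectivity requires rhythmic synchronization between pre and post synaptic neurons and their coherence" and describes alpha-tACS as entraining alpha oscillations. The Discussion expects the EEG to show connectivity change inside the brain, to relate it to cognitive performance, and to describe brain changes, "namely connectivity across proximal and distal regions".

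**The concern.** Two scalp electrodes can show coherence because both pick up the same generator, through volume conduction or a common reference, with no interaction between the tissue beneath them. That part of coherence depends on how strong the alpha signal is against the background. The combined arm and the SoP arm differ by active tACS at the participant's own alpha frequency, so a difference in alpha power between them is plausible. Randomisation does not remove it, because the power difference would itself be an effect of treatment.

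At stake is the reading of the mechanistic result. A higher electrode coherence in the combined arm could be reported as restored communication in the disconnected-brain framework, when a stronger alpha signal alone might have produced it. The text has no step that separates the two readings.

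**Working it through.** **Inputs.** From the protocol: analysis between eight scalp electrodes; alpha power recorded from the same EEG; active tACS in one of the two arms compared. The protocol gives no figure for coherence, leakage or alpha power, so there is none to reproduce. All gains, noise levels and power changes below are assumptions.

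**One-source model.** Electrodes 1 and 2 record g1·s + e1 and g2·s + e2. The alpha source s has power P, and e1 and e2 are independent with unit power. There is no interaction between regions. The cross-spectrum is g1·g2·P, so magnitude-squared coherence is

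C = [g1²P/(g1²P+1)] × [g2²P/(g2²P+1)].

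Doubling P gives:

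| Gains g1, g2 | P before → after | C before | C after |
|---|---|---|---|
| 1, 1 | 1 → 2 | 1/2 × 1/2 = 0.25 | 2/3 × 2/3 = 0.44 |
| 1, 0.5 | 1 → 2 | 1/2 × 0.25/1.25 = 0.10 | 2/3 × 0.50/1.50 = 0.22 |
| 1, 0.2 | 1 → 2 | 1/2 × 0.04/1.04 = 0.02 | 2/3 × 0.08/1.08 = 0.05 |
| 1, 0.2 | 32 → 64 | 32/33 × 1.28/2.28 = 0.54 | 64/65 × 2.56/3.56 = 0.71 |

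The direction is the same in every row. The size depends on the leakage and on the alpha-to-noise ratio, as the last two rows show.

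**Two uncoupled generators**, each of power P, leakage 0.3 both ways, unit noise: C = (0.6P)²/(1.09P+1)². For P = 1 this is 0.36/2.09² = 0.08; for P = 2 it is 1.44/3.18² = 0.14.

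**Cases where coherence does not rise.**
- Same two generators without sensor noise: 0.36/1.09² = 0.30 at any P.
- Uncoupled generators with no leakage: 0 at any P.
- Extra alpha of power Q seen by one electrode only, added to the equal-gain case: 1/2 × 1/(2+Q), which falls from 0.25 at Q = 0 to 0.17 at Q = 1.

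**A zero-lag-insensitive measure.** In the uncoupled models the cross-spectrum is real, so the imaginary part of coherency is zero in theory. A simulation with 200,000 segments gave 0.000 to 0.002 at every alpha power. With a fixed true coupling of 0.3 at a phase lag of π/4 and leakage 0.3, doubling power moved the imaginary part from 0.085 to 0.111, while ordinary coherence went from 0.15 to 0.25. The false coupling is removed, but some dependence on signal-to-noise remains.

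**The case against.** The strongest objection is that this is a condensed article. The connectivity sentence lists coherence and connectivity side by side and uses a toolbox whose footnote is not shown. The estimator, the reference and the handling of lag may be set in a fuller plan. This stands in part: one may not infer that connectivity is defined as coherence and nothing else. But the article does commit to analysis between electrodes, names coherence, and draws conclusions about brain regions, so the point concerns a stated method as well as missing detail.

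Other objections also limit the point:
- A rise in alpha power is not a stated aim. The Introduction speaks of entrainment and of increasing connectivity, and alpha power is listed without a direction. The power difference is an inference.
- A reader might infer that coherence must rise with alpha power. It need not, as the exceptions show.
- A reader might infer that the mechanistic aim cannot be answered, or that eight electrodes rule out any separation. Alpha power is measured separately in the same recordings, so the data allow further analysis, and nothing in the document shows that eight channels are too few.
- The correlations with UFOV and EXAMINER change under Long-Term Effects cover alpha power, desynchronization and phase-amplitude coupling, not coherence. The link from connectivity to performance rests on the general statement in the Discussion.
- Against the active-tACS-alone arm, both groups receive active stimulation, so a power change due to tACS itself would occur in both. The ambiguity falls mainly on the contrast with SoP alone.
- Change in alpha power arises after randomisation and may be part of the mechanism. Adjusting for it could remove a real effect.

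**Conclusion.** The point holds as an ambiguity of interpretation. As written, the plan does not separate better coupling from stronger shared alpha when electrode coherence differs between the combined and SoP arms. If alpha power doubled with no change in coupling, the one-source model gives rises from 0.02 to 0.05 at the low end and from 0.25 to 0.44 with equal gains, at an alpha-to-noise ratio of 1. Higher assumed ratios can give larger baselines and shifts. None of these is an estimate for this trial: they rest on assumed pickup, noise and power change, and the sign itself depends on the configuration.

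The documents do not support saying that the trial is unable to answer its mechanistic question. The trial is described as exploratory and resting EEG as a surrogate outcome. The UFOV primary, its sample size and the EXAMINER analysis are not affected. The change is worth making because connectivity is a stated aim and the remedy is cheap.

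**What to change.** In Statistical Analysis, EEG Data:
- Pre-specify one measure insensitive to zero-lag mixing, either the imaginary part of coherency or the weighted phase-lag index, in the individual alpha band and on the same recordings. Make it the measure on which any connectivity claim rests.
- Report ordinary electrode coherence descriptively, next to the alpha-power change in each arm. Keep any power-adjusted analysis as a sensitivity analysis only.
- In the Discussion, limit the conclusion to coupling between the recorded scalp sites.

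The cost is an analysis script and some wording, with no new data. The downside is that these measures discard genuine zero-lag coupling and do not remove every signal-to-noise effect, so the alpha-power change should still be shown beside them.

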**Figure 3 F3:**
[figure not shown]
Schematic representation of the overall procedure, including session procedure. Follow-up assessments will start 1 month after the intervention has ended.

##### Long-Term Effects

Assessments at 3 and 6 months of follow-up will be critical for understanding the longterm effects of the intervention. We will use the reliable change index (RCI; Ferguson et al., 2002) for the primary (i.e., UFOV) and secondary endpoints such as the NIH EXAMINER. By assessing if the changes in test scores are reliable across those time points, our understanding about the long lasting effects of the intervention will improve, while potential placebo effects that are not expected to persist for that long will be mitigated. This will be performed by means of Chi-squares, with time as within subject factor and intervention as between subject factor. At the 1, 3, and 6 month follow-ups, participants will also perform the EEG, in order to allow for the correlation between changes in α- power, Event Related Desynchronization (ERD; for alpha attenuation), Phase amplitude coupling (PAC; mainly α−γ) and with the reliable change indexes (RCI) from the primary (UFOV) and secondary outcomes (NIH EXAMINER), which will increase our understanding about the mechanisms underlying this intervention.

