In this sense, alpha tACS (α-tACS) may be a suitable combination for SoP training. For instance, α-tACS induces preferential phase synchronization of fast spiking neurons, thus resulting in an entrainment process of alpha oscillations (Huang et al., 2021). Moreover, alpha band is thought to work as a brain timer, setting up excitation and/or inhibition microstates, which will optimize incoming information processing or inhibition (Mathewson et al., 2011). Furthermore, α-tACS is able to modulate temporal resolution of human vision by acting over the segregation/integration time window of visual information, thus inducing participants to integrate more often two stimuli into one percept (Battaglini et al., 2020); or even to modulate information transfer in the premotor-cerebellar loop during learning (Schubert et al., 2021).

Interestingly enough, alpha activity seems to be one of the most distinguishable alterations in the human brain due ageing, with several studies showing changes in terms of alpha power, coherence and peak frequency in older adults, when comparing to younger ones (Purdon et al., 2015; Beese et al., 2019; Elshafei et al., 2020).

Here the goal is to use each participant’s endogenous peak alpha frequency to guide endogenous alpha phase-tACS (α-tACS) to further increase brain connectivity within brain networks (Bächinger et al., 2017).

In this sense, the current proposal aims to combine two interventions that have already shown promising results: a specific SoP training that has been shown to produce results in the elderly (Edwards et al., 2017) and an intervention that has been shown to entrain brain activity (Huang et al., 2021), as a means of increasing brain connectivity (Bächinger et al., 2017).

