### Statistical Analysis

#### Primary Outcome

We expect that all groups, after the intervention, have increased performance in the UFOV scores, however we also expect that the group with the combined active α-tACS and SoP training would present the largest increase in scores, when comparing to either intervention alone. This will be tested by calculating the delta (week 3 or 6—baseline), and by performing independent one-way ANOVAS with intervention as a factor. Moreover, with the present design, we can track the intervention effects in several time points, namely between baseline, at week 3 and 6 of the interventions. This will be performed by means of an exploratory mixed model-ANOVAS, with time as within subject factor and intervention as between subject factor. As we cannot control at this point for several variables such as gender, depression or years of education, if there are significant differences between groups after randomization, we will include those covariates in the analysis, performing ANCOVAS instead of ANOVAS.

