#### Secondary Outcomes

##### NIH Examiner

The NIH EXAMINER battery is important to address transfer effects to untrained domains, such as executive function, insight or social cognition and behavior. Chi-square tests will be used for week 3 and 6 reliable change indexes. Reliable Change Index (RCI) will be calculated by using the standard deviation of the reference data-set, and the test-retest reliability (Cronbach’s alpha). As we want the RCI, the difference between measurements will be compared to the S_Diff_ multiplied by 1.96 (Jacobson and Truax, 1991). This will allow for a categorial YES/NO variable for the chi-square tests. Moreover, with the present design, we can track the intervention effects in several time points, namely at baseline, week 3 and 6 of the treatment. This will be performed by means of chi-squares, with time as within subject factor and intervention as between subject factor.

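### The planned correlation of EEG change with the reliable change indexes names no arm term, so if it is run over all participants it can mix differences between arms with individual-level association

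*Protocol article*

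**What the plan says.** Under Long-Term Effects, EEG is repeated at the 1, 3 and 6 month follow-ups "in order to allow for the correlation between changes in α- power, Event Related Desynchronization" and phase amplitude coupling, on one side, and the reliable change indexes of UFOV and NIH EXAMINER on the other. The stated purpose is mechanistic: "which will increase our understanding about the mechanisms underlying this intervention". The Discussion repeats the aim: "we want to explore how changes in cognition are related to changes in the brain, as assessed by the EEG".

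The correlation is given no arm term, within-arm analysis or mediation model. The method sentence just before it does carry one, but for a different test: "This will be performed by means of Chi-squares, with time as within subject factor and intervention as between subject factor".

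Elsewhere the article expects treatment to move both sides of the correlation. For UFOV, Primary Outcome expects that "the group with the combined active α-tACS and SoP training would present the largest increase in scores". For EEG, the Introduction describes tACS as "an intervention that has been shown to entrain brain activity", and Outcomes treats resting EEG as a surrogate outcome. The Discussion confirms that there is no double-sham arm. The arms are the combination, SoP alone and tACS alone.

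**The concern.** The mechanistic question is whether participants whose EEG changes more also improve more. Two arms receive active tACS, meant to change alpha, and two receive active SoP training, meant to change UFOV, but they are not the same two arms. A correlation over all participants then has two sources: association within arms, and covariance between the arm means.

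The second source can mislead in either direction. If tACS alone drives alpha and SoP alone drives UFOV, the arm means pull the correlation negative, which can hide a real positive link. If only the combination improves UFOV, they pull it positive and can suggest a mechanism where no individual link exists. In both cases the result partly restates the treatment contrasts.

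**Working it through.** **Planning figures (Sample Size).** The article states no figure for the correlation, so its sample size serves only to set n and a plausible effect. The standardised difference is d = (56.2 − 31.5) / √[(74.8² + 43.7²)/2] = 24.7 / 61.26 = 0.403. A two-sided two-sample t-test at alpha 0.05 and power 0.80 needs 97.5, so 98 per group. 98/0.9 = 108.9, so 109, and 3 × 109 = 327. All agree with the article.

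**Assumptions.** There are 98 per arm (294 in total). Change scores have within-arm SD 1 and are oriented so that improvement is positive. The arm shifts and the within-arm correlation are assumed, because the article gives none.

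**Between-arm covariance.** Order the arms as combination, SoP alone, tACS alone. Let the EEG shifts be (a, 0, a) and the UFOV gains (gC, gS, gT). Then

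cov = a(gC + gT)/3 − (2a/3)(gC + gS + gT)/3 = a(gC + gT − 2gS)/9.

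- Additive, gains (g, g, 0): −ag/9.
- Only the combination gains, (g, 0, 0): +ag/9.
- Graded, gains (0.8, 0.4, 0): a(0.8 − 0.8)/9 = 0.

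If the combination alone is shifted by s on both variables, the covariance is s²/3 − s²/9 = 2s²/9. In the additive pattern with a = g = s it is −s²/9. In both patterns each variable has total variance 1 + 2s²/9.

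**Expected overall correlation at s = 0.8**, where 2s²/9 = 0.1422 and s²/9 = 0.0711:

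- Combination alone shifted on both, no link: 0.1422/1.1422 = 0.125.
- Additive, no link: −0.0711/1.1422 = −0.062.
- Additive, true within-arm r = 0.2: (0.2 − 0.0711)/1.1422 = 0.113.

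**Check by Fisher's z**, with √(294 − 3) = 17.06:

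- 0.125 gives z ≈ 2.14, so rejection of about 57%.
- −0.062 gives |z| ≈ 1.06, so about 19%.
- 0.113 gives z ≈ 1.93, so power of about 49%.
- With arm in the model, r = 0.2 gives 0.2027 × √289 = 3.45, so power of about 93%.

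**Simulation** (10,000 trials per setting, two-sided 0.05, continuous index):

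| Setting | s = 0.4 | 0.6 | 0.8 | 1.0 |
|---|---|---|---|---|
| No link, combination alone shifted on both: false rejection | 9% | 25% | 58% | 89% |
| No link, additive: false rejection | 6% | 10% | 19% | 33% |
| True r = 0.2, additive: power without arm term | 86% | 72% | 49% | 23% |
| True r = 0.2, additive: power with arm term | 93% | 93% | 94% | 94% |

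If tACS shifts EEG by 0.8 SD in both its arms but only the combination gains 0.8 SD on UFOV, false rejection is again about 19%. With the arm term, false rejection stayed at 4.5–5.4% in every setting.

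**Patterns without inflation.** EEG shifts of 0.4/0/0.4 with UFOV gains of 0.8/0.4/0 gave 5%. A shift in EEG alone also gave 5%.

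**YES/NO index.** NIH Examiner describes a dichotomised index: "This will allow for a categorial YES/NO variable for the chi-square tests". Cutting at 1 SD (an assumption), false rejection with the combination alone shifted is 7% at 0.4 SD and 41% at 0.8 SD. Additive power at 0.8 SD is 33%, against about 74% with the arm term. Cutting at 1.96 instead, with UFOV gains of 0.8 SD and alpha shifts of 0.5 to 1.2 SD, gives false rejection of 6–11%. The direction is the same, but the size depends on the cut.

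**The case against.** The strongest reply is that this is a condensed article on a trial it labels exploratory. The sentence mainly explains why EEG is collected at follow-up, and a full analysis plan could specify a within-arm or partial correlation. This stands in part. A reader might infer that the plan commits to pooling all participants, or that the mechanism will be decided by this test. The text supports neither: it does not say the arms are pooled, and it gives no alpha or decision rule for the correlation. What remains is that it names a statistic and the inference to be drawn from it, and attaches the intervention factor only to the neighbouring chi-squares.

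A reader might also infer that the result is biased whenever the treatments work. That goes too far. The bias needs arm to shift both variables in a related pattern, and a graded pattern that respects the article's own expectation (0.8/0.4/0) gives none. It also needs an EEG shift that is still present 1 to 6 months after stimulation ended, which the article neither quantifies nor claims. The masking case gives SoP alone the same gain as the combination, which is not what the article expects. At the planning effect of about 0.4 SD the distortion is small.

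The dichotomised index is described for the chi-square tests, so it need not apply to the correlation.

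Finally, adjusting for arm removes covariation induced by treatment and so answers a narrower question. That is fair. Because EEG change is not randomised, neither version establishes mechanism.

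**Conclusion.** The point holds in a limited form. The article plans a correlation of EEG change with the cognitive reliable change indexes to inform mechanism, and names no arm term. If it is run over all participants, it mixes individual-level association with differences between arm means whenever arm shifts both variables in a related pattern.

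With 98 per arm and assumed shifts, the distortion is slight at 0.4 SD. It becomes material at 0.8 SD in the additive and combination-only patterns, either as false association or as loss of more than 40 percentage points of power for a true within-arm correlation of 0.2. It is absent in other patterns. Its sign and size cannot be known in advance from the article.

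This is a near-free improvement to an exploratory analysis. The primary ANOVA on UFOV is not affected.

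**What to change.** Replace the correlation with a regression of the continuous UFOV (or NIH EXAMINER) change on the EEG change, with arm as a factor. This is equivalent to a within-arm partial correlation. Report the arm-by-EEG-change interaction as a check that the association is similar across arms, and describe the result as associational, not as proof of mechanism.

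The cost is a sentence or two in the analysis text and two degrees of freedom for arm, with no new data. If the full analysis plan already does this, stating it in the article's analysis section closes the point.
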